## Assessments

Assessments will be conducted at pre-treatment (T0) and at 9 weeks, 6- and 12-months follow-up (T1, T2, T3; see Table 1). All self-report assessments, potentially effect-modifying covariates and demographic variables will be provided using a web-based interface integrated into the intervention platform. Section A (Affective Syndromes) of the SCID [43], the Hamilton Rating Scale for Depression (HAM-D-17 [56]) and the Quick Inventory of Depressive Symptomatology (QIDS-C16; [57]) will be performed via telephone interviews at T0 and T3. Moreover, we translated the SCID-V-RV into German to be able to comment on DSM-IV and -V [58] diagnoses.

**Table 1 Tab1:** Outcome assessments and assessment time point

Variables	Measurement	Screening	T0	T1	T2	T3
Inclusion/exclusion criteria						
Chronic Back pain	MR + TI	x	x			
Depressive symptomatology	PHQ-9	x	x	x	x	x
Inclusion criteria a), c), d)	TI/SRQ		x			
Acute/past 6 months depressive episode, dysthymia or bipolar disorder	SCID		x			x
Current/past 6 months/on waiting list for psychotherapy	TI		x			
Suicidality	SCID/HAM-D/QIDS		x			x
	PHQ-9	x	x	x	x	x
Primary outcome						
Onset of Depression	SCID		x			x
Secondary outcomes						
Severity of depressive symptoms	PHQ-9	x	x	x	x	x
	HAM-D/QIDS		x			x
Quality of life	AQOL-6D/EQ-5D-5 L		x	x	x	x
Pain intensity	Rating scale		x	x	x	x
Pain related disability	ODI		x	x	x	x
Pain self-efficacy	PSEQ		x	x	x	x
Ability to work	SPE		x	x	x	x
Economic evaluation						
Costs	TiC-P		x		x	x
Quality of life	AQOL-6D/EQ-5D-5 L		x	x	x	x
Covariates						
Demographic variables	SRQ/MR	x	x			
Depression type and chronicity	SCID		x			x
Patient adherence	Attrition rate			x	x	
Patient satisfaction	CSQ-8^a^			x		
Side-effects of intervention	INEP^a^			x	x	
Back Pain type and chronicity	MR	x				
Internet affinity	IAS		x			

*AQol*-*6D* Assessment of Quality of Life, *CSQ*-*8* Client Satisfaction Questionnaire, *EQ*-*5D*-*5 L* European Quality of Life scale, *HAM*-*D* Hamilton Rating Scale for Depression, *IAS* Internet Affinity Scale, *INEP* Inventory for the Assessment of Negative Effects of Psychotherapy, *MR* Medical record, *ODI* Oswestry Disability Index, *PHQ*-*9* Patient Health Questionnaire, *PSEQ* Pain Self-Efficacy Questionnaire, *SCID* Structured Clinical Interview for DSM, *SPE* Subjective Prognostic Employment scale, *SRQ* Self-report assessment questionnaire, *TI* telephone interview, *TiC*-*P* Trimbos/iMTA questionnaire for costs associated with psychiatric illness

^a^intervention group only

Videos promoting the importance of collecting data will be implemented into online assessments to enhance compliance with completing measures. In psychological intervention trials, blinding of study participants and eCoaches is not possible. However, all members of the research team conducting telephone administered outcomes will remain blinded. Therefore, both participants and interviewers will be reminded of the reason and importance of blinding at the beginning of each interview. Moreover, performance bias will be minimized, as the web-based intervention is separated from other health care services.

### Secondary outcomes

#### Depressive symptoms

Depressive symptoms will be assessed by the self-administered Patient Health Questionnaire (PHQ-9) [64], a telephone-based clinician rating of the Hamilton Rating Scale for Depression (HAM-D-17), and the Quick Inventory of Depressive Symptomatology (QIDS) [56, 57]. The PHQ-9 is a well validated and widely used depression screening instrument [64] and has also been evaluated to be delivered as online-version [65]. The 17-item HAM-D is the most widely used clinician-rated measure of depression severity and as such viewed as the gold standard for the assessment of depression severity. The 16-Item QIDS will be used to further validate the depressive symptom outcome measures. It covers all criterion symptom domains of the DSM for diagnosing a MDD [57]. HAM-D and QIDS are administered to determine depression response [66].

#### Quality of life

To assess health-related quality of life, the Assessment of Quality of Life (AQoL-6D) will be used, which includes 20 items assessing the following dimensions: independent living, mental health, coping, relationships, pain, and senses [67]. Besides measuring health-related quality of life, the AQoL-6D is suitable for economic evaluations of health programs and has good psychometric properties [67]. It has also shown to be reliable, with a Cronbach’s alpha of .89 [68]. Because this is a relatively new instrument, we additionally will use the EuroQol (EQ-5D-5 L), the most widely used quality of life assessment, as a basis for cost-utility analyses [69]. The EQ-5D measures five health domains of importance to quality of life: mobility, self-care, usual activities, pain/discomfort, and anxiety/depression. The 5-level version includes five levels of response, which has been found to be more discriminative and to reduce ceiling effects compared to the 3-level version [70, 71].

#### Pain intensity and pain associated disability

Pain intensity and pain-related disability will be measured following the IMMPACT recommendations for core outcome measures for chronic pain clinical trials [72, 73]. Pain intensity will be measured by an 11-point numerical rating scale (0-10) of pain intensity as well as categorical classification of pain intensity (none, mild, moderate, severe). The Oswestry Disability Index (ODI) will be used to assess pain related disability. The ODI is a reliable and valid self-assessment questionnaire including 10 items [74].

#### Pain self-efficacy

Self-efficacy with regard to pain management will be assessed by using the Pain Self-Efficacy Questionnaire (PSEQ), which is a validated and reliable (internal consistency: α = 0.93) 10 item instrument that assesses self-efficacy expectations related to pain [75].

#### Work capacity

Work capacity will be assessed using the German version of the Subjective Prognostic Employment Scale (SPE), a validated 3-item self-report questionnaire with high internal consistency (Guttman scaling: rep = .99) [76].

#### Intervention satisfaction and adherence

Patient satisfaction with the intervention will be measured by using an adaptation of the Client Satisfaction Questionnaire (CSQ-8, German: ZUF-8), optimized for the assessment of client satisfaction with online interventions (CSWIQ-8) [77]. The CSQ-8 is a validated 8 item instrument with high internal consistency (α = 0.93) [78]. The adapted version, validated for the assessment of client satisfaction in web-based interventions, has been shown to have high internal consistency in a range of studies (α = 0.92-0.94) and is associated with treatment adherence and outcome [79–81]. The attrition rate (i.e. percentage of participants who no longer use the intervention assessed by their log in data) will give an estimate of the participants’ intervention adherence.

#### Side effects of psychotherapy

The German version of the Side Effects of Psychotherapy Inventory (INEP) [82] will be used to measure side-effects of psychotherapy. The INEP consists of 15 items assessing a range of common changes participants may have experienced due to the effects of the preventive intervention in their social and work environments.

#### Costs

To measure costs, the Dutch cost questionnaire: “Trimbos Institute and Institute of Medical Technology Questionnaire for Costs Associated with Psychiatric Illness” (TiC-P) [51], adapted for the German health care system, will be used [83]. The TiC-P is a widely used self-report questionnaire to measure health care consumption and productivity loss [84]. We further adapted the questionnaire for the population of chronic back pain patients. Participants will register all direct health service uptakes during the last 3 months, e.g. the number of general practice visits, sessions with psychiatrists, and hospital days. In addition, productivity-related costs will also be assessed. This includes the number of ‘work loss’ days (absenteeism), the number of ‘work cut-back’ days (presenteeism), and costs associated with for domestic tasks. Estimated development costs as well as opportunity costs will be included in the economic evaluation.

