## Intervention

### Intervention condition

The intervention (eSano BackCare-DP) consists of six weekly sessions plus three optional modules and two booster sessions of approximately 45 to 60 min each (see Figs. 2 & 3). Participants can decide when to complete the booster sessions at the end of the last session. They can choose two dates within a timeframe of 3 months following the intervention, and will be reminded to log-in again. Sessions can be repeated as often as desired. All modules consist of information about depression and (chronic) back pain, provided by text, audio, and video, as well as assignments, metaphors and exercises. The content of the intervention is based on cognitive behavioral therapy (CBT) for depression, including elements of psychoeducation, social skills, problem solving, behavioral activation, improving self-care, relaxation and motivation for physical exercises. The intervention is based on prior interventions that have been evaluated in a number of RCTs in different samples [31, 34, 44–46]. We adapted and substantially extended the predecessors to the context of depression prevention and chronic back pain. In order to address chronic back pain patients specifically, psychological pain intervention elements are integrated in every module of the intervention. Moreover, three optional modules are offered, focusing on problems with sleep, partnership/sexuality and returning to the workplace. Emphasis is laid on homework assignments, which are intended to provide practice of learned skills. To enhance patient adherence, interactive elements (quizzes, conditional contents) are implemented. Participants will be asked about adverse events at the beginning of every session with the advice to check whether it is the right time to go on with the session. The intervention platform is provided by Minddistrict (www.minddistrict.com), a company specialized in the provision of web-based health interventions. Access to the platform proceeds through a unique username-password combination and will be available on a 24/7 basis. All transferred data will be secured based on ISO27001 and guidelines NEN7510.

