### Control condition

Participants of the control condition will have unrestricted access to TAU. Although national treatment guidelines for low back pain and depression exist [50], TAU following orthopedic rehabilitation care may vary. There is no minimum treatment defined and TAU will not follow a standardized protocol; however, all received types of medical/psychological help during the last 3 months will be monitored with the Trimbos/iMTA questionnaire, to account for all costs associated with psychiatric illness (TIC-P) [51]. Using these data, an accurate description of TAU can be provided.

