### Economic evaluation

Baseline utilities and costs will be compared between both groups and if necessary, statistical techniques will be used to adjust for baseline differences [89]. In the cost-effectiveness analysis, the incremental cost-effectiveness ratio (ICER) will be presented as costs per depression-free year (DFY) gained. DFYs will be based on the number of depression-free weeks up to onset of a major depressive episode within the 12-month follow-up period. The ICER in the cost-utility analysis will be stated as costs per quality-adjusted life year (QALY) gained. Non-parametric bootstrapping (2500 times) will be applied to estimate the robustness of the ICERs and to quantify the uncertainty around the ratios. The bootstrapped replicates of the ICERs will be graphically represented in a cost-effectiveness plane, with effects along the horizontal axis and costs along the vertical axis.

In addition, a cost-effectiveness acceptability curve will be graphed to assess the probability that the intervention is more cost-effective relative to treatment as usual at varying willingness-to-pay (WTP) ceilings.

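### The cost questionnaire's 3-month recall covers health-service use for only 6 of the 12 follow-up months, and adjustment for baseline costs and utilities is left to an undefined look at the data

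*Protocol article*

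**What the plan says.** The Costs section of the protocol article gives the recall period: "Participants will register all direct health service uptakes during the last 3 months". The Control condition section repeats it ("all received types of medical/psychological help during the last 3 months will be monitored") and concludes: "Using these data, an accurate description of TAU can be provided".

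The assessments are T0 (pre-treatment), T1 (9 weeks), T2 (6 months) and T3 (12 months). In Table 1 the TiC-P is marked at T0, T2 and T3 and not at T1. The two quality-of-life instruments are marked at all four times.

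On productivity, the Costs section says "In addition, productivity-related costs will also be assessed" and gives no recall window. The Guidance section records eCoach time per participant for the economic analysis, and the Costs section also includes development and opportunity costs.

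The Economic evaluation section plans cost per depression-free year over the 12-month follow-up and cost per QALY, with 2500 bootstrap replicates. It compares baseline utilities and costs between the groups and adds: "if necessary, statistical techniques will be used to adjust for baseline differences". No criterion for necessity is given.

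**The concern.** Effects are measured over the whole year, but the service-use part of the cost difference is measured over half of it. The first gap coincides with the main phase of the intervention and the first months of aftercare, when the programme is most likely to trigger or replace other care. An analysis plan can say how to fill unobserved months, but it cannot recover service use that nobody was asked about. The schedule and recall period are therefore design choices that have to be put right in the design.

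The baseline rule is a separate weakness in the same analysis. If the baseline comparison decides whether adjustment is made, the data choose the estimator of the incremental cost and the incremental QALY. Imbalances that do not trigger adjustment stay in the estimate, and precision available from data already collected is lost.

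Cost-effectiveness is one of the trial's stated hypotheses, so both points bear on a main claim. Neither touches the primary endpoint.

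**Working it through.** The plan states no figure here to reproduce. The coverage check uses the plan's own schedule; the imbalance check needs assumptions, labelled below.

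**Coverage of health-service use**

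Inputs: recall of 3 months (Costs; Control condition); TiC-P at 0, 6 and 12 months (Table 1). An assessment at month t covers months t−3 to t.

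| Assessment | Months covered | Months since randomisation observed |
|---|---|---|
| T0 | −3 to 0 | 0 |
| T2 | 3 to 6 | 3 |
| T3 | 9 to 12 | 3 |

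Observed: 3 + 3 = 6 of 12 months (50%). Not asked about: months 0–3 and 6–9.

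**Position of the intervention**

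The programme "consists of six weekly sessions plus three optional modules and two booster sessions of approximately 45 to 60 min each". Six weeks is 42/30.44 = 1.4 months, so the weekly modules fall wholly in the first gap if completed on schedule. Boosters can be placed within 3 months after the modules, about months 1.4 to 4.4. Those from month 3 onwards lie inside the T2 recall.

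**What extrapolation can recover**

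Suppose, for illustration, that the arms differ by EUR 200 in months 0–3 and by nothing afterwards. The true 12-month difference is 200 + 0 + 0 + 0 = EUR 200. Doubling the two observed quarters gives 2 × (0 + 0) = EUR 0. Interpolating between T0 and T2 does no better: T0 precedes randomisation and carries no treatment effect, so in expectation the interpolated difference is also zero.

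**What changes to the schedule would give**

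- Recall at T2 and T3 back to the previous cost assessment (6 months): 12 of 12 months.
- TiC-P added at T1 only: 9 weeks is 63/30.44 = 2.07 months; 6 + 2.07 = about 8.1 of 12 months, leaving about 3.9 uncovered, including all of months 6–9.

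**Conditional baseline adjustment**

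Inputs: 203 per group (Sample size/power calculation). Assumptions: adjustment is triggered at two-sided p<0.05; the correlation r between the baseline value and the 12-month outcome is 0.3 to 0.7.

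- SE of the baseline difference, in SD units: √(2/203) = 0.0993.
- Largest imbalance left unadjusted: 1.96 × 0.0993 = 0.195 SD.
- Part carried into the follow-up difference, r × 0.195: 0.058 SD at r = 0.3, 0.097 at r = 0.5, 0.136 at r = 0.7.
- Variance removed by adjustment, r²: 0.09 at r = 0.3, 0.25 at r = 0.5, 0.49 at r = 0.7.

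The carried-over values are those at the trigger threshold, not expected errors.

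**The case against.** The strongest reply is that the article does not say how 12-month costs are built from the windows, and may properly leave that to the full protocol or analysis plan. That stands against one tempting inference, that the recorded windows will simply be added and service costs halved. Nothing in the document says so, and with steady costs ordinary extrapolation would remove that error. It does not answer the gap itself, because no fill-in rule can see a difference that occurs only in unobserved months.

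A reader might also infer that the cost of the intervention is missed, or that half of all costs are. Neither is supported. Guidance time is logged separately, development and opportunity costs are included, some boosters fall within the T2 recall, and the 3-month window is stated only for health services and not for productivity loss.

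On baseline adjustment, it is fair to say that adjustment is foreseen, that a method is cited which cannot be seen here, and that 1:1 randomisation keeps the unadjusted increment unbiased on average. This rules out saying that the ratios rest on chance imbalance. Nor can the imbalance be called as large as the likely QALY gain, since the documents give no expected gain. The undefined trigger and the lost precision remain.

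**Conclusion.** The point holds in a limited form. From the plan's own schedule and recall period, health-service use is observed for 6 of the 12 months after randomisation and is unobserved in months 0–3 and 6–9. This needs no outside figure. It applies to service use other than the intervention; for productivity loss the article does not allow a conclusion. How far it would move the cost difference cannot be sized from the documents, because that depends on any arm difference specific to the gaps. The claim that treatment as usual can be accurately described is too strong for those months.

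The baseline rule is a stated, data-driven choice of estimator of modest consequence: at most about 0.06–0.14 SD carried into follow-up without triggering adjustment, and about 9–49% of variance forgone. Both ranges rest on the assumed correlations; the first also rests on the assumed p<0.05 trigger. Both matters should be corrected for the economic evaluation.

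**What to change.** 1. Adjust incremental costs and QALYs by regression for baseline cost and baseline utility within every bootstrap replicate, whatever the baseline comparison shows. This is a wording change; the data are already collected.

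2. For assessments still to come, make the cost windows join. Extending TiC-P recall at T2 and T3 back to the previous cost assessment gives full coverage, at the price of less accurate recall. Adding the TiC-P to the existing T1 online assessment, asking about the time since baseline, costs a small extra burden but alone reaches only about 8.1 of 12 months. The two can be combined. Participants already past these assessments will lack the added coverage.

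3. For participants with uncovered months, fill them from the post-randomisation windows and not from T0 recall alone: participants are recruited after orthopaedic rehabilitation, so that recall may include the stay. Add a sensitivity analysis that varies the arm difference in the unobserved months, and report those months as a limitation. This is analysis and reporting wording.

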#### Covariates

As potentially effect-modifying covariates, demographic variables (gender, age, education), social support and medical variables (prior pain and depression treatments) will be assessed via self-report at baseline. Internet competencies will be assessed by the Internet Affinity Scale [85]. The translated version by Haase and colleagues [86] will be used. Back pain type, severity and chronicity will be extracted from medical records.

## Statistical analysis

### Clinical analyses

All analyzes will be performed according to the intention-to-treat (ITT) principle. Kaplan-Meier curves and Cox proportional hazard regression analysis will be used to determine differences in time to onset of MDD in weeks between both study conditions over a follow-up period of 12 months. The dependent variable will be time to onset of MDD and treatment condition will be the independent variable. The proportional-hazards assumption will be tested based on the scaled Schoenfeld residuals test. Survival analysis assumes that censoring (i.e., a participant is lost-to-follow-up or completes the follow-up period without experiencing a major depressive episode) is non-informative. Non-informative implies that the reasons why participants drop out of the trial are unrelated to the study condition (i.e., participants in one study arm should not be routinely censored). We will apply the following methods to deal with informative censoring, if necessary: (a) imputation techniques for missing data, (b) sensitivity analyses to illustrate best and worst case scenarios to test the robustness of the base case findings and (c) the use of the drop-out event as a study end point [87]. In addition, the number needed-to-treat (NNT) to prevent one additional event in the intervention group versus the control group will be calculated [88]. Covariates will first be checked whether they are associated with the primary outcome, if not left out of the final analysis.

Secondary outcomes will be analyzed using hierarchical linear modeling. To examine potentially moderating covariates, correlation of covariates and outcome parameter are analyzed using multiple regression models. In addition, per protocol analysis will be performed to investigate the influence of drop-outs on study results. Missing data will be imputed using multiple imputation. Potential confounding factors between source population and study population will be assessed, which enables us to evaluate the external validity of the sample. Finally, characteristics of dropped out participants at follow-up will be inspected and resulting socio-demographic differences between intervention and control group will be described. A significance level of *p* ≤ .05 will be set for all analyses.

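### Non-informative censoring is defined as drop-out unrelated to study arm instead of to time to MDD, and the primary-outcome remedies are conditional on that definition

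*Protocol article*

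**What the plan says.** The Clinical analyses section of the Protocol article sets Kaplan-Meier curves and Cox regression for time to onset of MDD. It counts as censored anyone of whom it can be said that "a participant is lost-to-follow-up or completes the follow-up period without experiencing a major depressive episode". It then explains the assumption: "Non-informative implies that the reasons why participants drop out of the trial are unrelated to the study condition", with the gloss that "participants in one study arm should not be routinely censored".

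The remedies follow under a condition: "We will apply the following methods to deal with informative censoring, if necessary". They are imputation, "sensitivity analyses to illustrate best and worst case scenarios", and "c) the use of the drop-out event as a study end point".

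The next paragraph opens with the secondary outcomes. It states without condition that missing data will be multiply imputed, adds a per-protocol analysis, and says that characteristics of drop-outs will be inspected and that "resulting socio-demographic differences between intervention and control group will be described".

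On measurement, the Assessments section says that the SCID and the two clinician-rated depression scales "will be performed via telephone interviews at T0 and T3". The Primary outcome section dates onset with life charts covering the follow-up period. Table 1 shows the PHQ-9 at T0, T1, T2 and T3.

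**The concern.** Drop-out may depend on arm and still be harmless to the Cox estimate, because arm is in the model. What biases the estimate is drop-out that depends on whether or when a participant develops MDD, beyond what arm and covariates explain. The article's sentence puts the test in the wrong place, and the trigger for the primary-outcome remedies depends on it. An analyst who followed the text could see similar drop-out in the two arms, conclude that nothing further was necessary, and report the unadjusted Cox result.

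This trial is exposed to the problem. The diagnosis is made by one interview at 12 months, so a participant who misses it contributes no onset, whatever happened during the year. The planned description of drop-outs names socio-demographic differences but not depression severity, although the PHQ-9 at 9 weeks and 6 months is the most direct evidence available on whether those lost were becoming depressed. At stake are the primary hazard ratio, the 12-month risk difference and the NNT.

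**Working it through.** **Inputs from the Sample size section:** control risk 0.20; absolute reduction 0.09, so intervention risk 0.11; hazard ratio 0.522; 64 events; 203 per arm; attrition 20%.

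**Assumed, not in the documents:** the share of onset cases that miss T3, d_e, is 40% to 50% in an affected arm and 20% in an unaffected arm. Overall drop-out is held at 20% in each arm unless stated. A participant without a T3 interview contributes no information on onset.

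**The plan's own figure.** ln(1 − 0.11)/ln(1 − 0.20) = 0.522, which reproduces the article.

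**Formula.** With true risk p and drop-out d_e in onset cases and d_n in the others, the observed risk is r = p(1 − d_e)/[p(1 − d_e) + (1 − p)(1 − d_n)]. When overall drop-out is 20%, the denominator is 0.80. The observed hazard ratio is ln(1 − r_int)/ln(1 − r_con).

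**Is independence from arm necessary? No.** Let drop-out be 10% in one arm and 30% in the other, unrelated to onset. Then d_e = d_n within each arm, r = p in both, and the hazard ratio stays at 0.522. The article's wording would call this informative.

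**Is it sufficient? No.** Let both arms lose onset cases by the same mechanism.

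| d_e, both arms | r control | r intervention | Hazard ratio | Risk reduction | NNT |
|---|---|---|---|---|---|
| 20% (unrelated) | 0.200 | 0.110 | 0.522 | 9.0 points | 1/0.09 = 11 |
| 40% | 0.20 × 0.60/0.80 = 0.150 | 0.11 × 0.60/0.80 = 0.0825 | 0.530 | 6.8 points | 1/0.0675 = 15 |
| 50% | 0.20 × 0.50/0.80 = 0.125 | 0.11 × 0.50/0.80 = 0.0688 | 0.533 | 5.6 points | 1/0.05625 = 18 |

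Drop-out here is unrelated to arm in both rate and reason, so the article would call it non-informative. The hazard ratio barely moves, but incidence, risk reduction and NNT are distorted.

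**Mechanism in one arm only, drop-out still 20% in each arm.**
- True hazard ratio 1.00 (risk 0.20 in both arms), intervention arm affected: r_int = 0.150 or 0.125 against 0.200. The hazard ratio is ln(0.85)/ln(0.80) = 0.73, or ln(0.875)/ln(0.80) = 0.60.
- True hazard ratio 0.522, control arm affected: ln(0.89)/ln(0.85) = 0.72, or ln(0.89)/ln(0.875) = 0.87.

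The bias can therefore favour either arm, and a comparison of drop-out frequencies would show nothing.

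**Best and worst case.** 41 of 203 are missing per arm and 162 observed, with 0.20 × 162 = 32.4 and 0.11 × 162 = 17.8 events.
- Best: 17.8/203 = 8.8% against (32.4 + 41)/203 = 36.2%, a difference of −27 points (hazard ratio 0.20).
- Worst: (17.8 + 41)/203 = 29.0% against 32.4/203 = 16.0%, a difference of +13 points (hazard ratio 1.97).

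**Drop-out as an endpoint.** 0.20 × 406 = 81 drop-outs against 64 planned MDD events. If drop-out is unrelated to onset, the composite risks are 1 − 0.80 × 0.89 = 0.288 and 1 − 0.80 × 0.80 = 0.360. The hazard ratio is then ln(0.712)/ln(0.640) = 0.76 when the true value is 0.522. With 25% drop-out in the intervention arm and 15% in control, the risks are 1 − 0.75 × 0.89 = 0.333 and 1 − 0.85 × 0.80 = 0.320, and the hazard ratio is 1.05.

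**The case against.** The strongest reply is that the article speaks of the reasons for drop-out, not only of its frequency. If depression-related loss acts in one arm and random loss in the other, the reasons differ by arm, and a literal reader would call that informative. The cases that bias the hazard ratio are therefore covered by the wording, and the case it plainly misses, a shared mechanism, leaves the hazard ratio at about 0.53. This stands as far as it goes. However, the gloss about one arm being routinely censored points the reader to frequency, and the shared case still distorts the risk reduction and the NNT, which the article plans to report.

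Second, a reader might infer that the primary outcome has no imputation unless the trigger is met, or that the remedies could not reveal the bias. The documents do not support either. Imputation is the first listed remedy, and the unconditional multiple-imputation sentence sits in a paragraph that also sets the significance level for all analyses. Its scope is ambiguous. What stands is that a conditional and an unconditional statement need reconciling.

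Third, a reader might infer that the article sets a formal test of drop-out balance that would pass while the estimate was biased. It sets none; it gives a definition, a condition and a description of drop-outs. The detailed trigger, the imputation predictors and the censoring date for those lost early may properly be in an analysis plan that is not shown, and their absence is not part of this point.

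Fourth, best/worst-case bounds are meant to be extreme. That they run from −27 to +13 points makes them uninformative around −9, but it is not an error. The drop-out endpoint rests on a cited source that cannot be seen here, and is one of three options.

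**Conclusion.** The definition is wrong as stated, and it is the only criterion the article gives for applying the primary-outcome remedies. It should be corrected before outcome data are examined.

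The size depends on how drop-out works, which the documents cannot show. If 40–50% of onset cases are lost in both arms alike, the hazard ratio is close to right and the harm falls on incidence, risk reduction and NNT. If the loss is confined to the intervention arm, a null effect can look like 0.73 to 0.60 with equal drop-out rates. It would be too strong to say that the primary hazard ratio will be biased, because that requires a mechanism that differs by arm. All of these figures assume that participants without a T3 interview contribute nothing on onset.

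Drop-out as an endpoint should not be used to judge the preventive effect. Drop-outs would outnumber MDD onsets, and the result would largely describe retention.

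**What to change.** - Restate the assumption: drop-out is independent of time to MDD onset, given arm and the modelled covariates. Remove the gloss about arms.
- Delete the condition *if necessary*.
- Reconcile the two imputation statements by saying that multiple imputation covers the primary outcome for every participant without a T3 SCID, by arm, using the baseline, T1 and T2 PHQ-9.
- Compare drop-outs with completers on baseline and interim PHQ-9 as well as on socio-demographic variables.
- Because multiple imputation assumes that data are missing at random, add a delta-adjusted tipping-point analysis, raising the imputed hazard in drop-outs stepwise by arm. The best/worst-case bounds can stay beside it.
- Do not use option (c) to judge the preventive effect.

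The cost is a paragraph of wording and some extra analysis. Every variable needed is already in Table 1.
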